## Abstract

**Background:**

Siewert type II adenocarcinoma of the esophagogastric junction (Siewert II AEG) can be resected by the right thoracoabdominal surgical approach (RTA) or abdominal-transhiatal surgical approach (TH) under minimally invasive conditions. Although both surgical methods achieve complete tumor resection, there is a debate as to whether the former method is superior to or at least noninferior to the latter in terms of surgical safety. Currently, a small number of retrospective studies have compared the two surgical approaches, with inconclusive results. As such, a prospective multicenter randomized controlled trial is necessary to validate the value of RTA (Ivor-Lewis) compared to TH.

**Methods:**

The planned study is a prospective, multicenter, randomized clinical trial. Patients (n=212) with Siewert II AEG that could be resected by either of the above two surgical approaches will be included in this trial and randomized to the RTA group (n=106) or the TH group (n=106). The primary outcome will be 3-year disease-free survival (DFS). The secondary outcomes will include 5-year overall survival (OS), incidence of postoperative complications, postoperative mortality, local recurrence rate, number and location of removed lymph nodes, quality of life (QOL), surgical Apgar score, and duration of the operation. Follow-ups are scheduled every three months for the first 3 years after the surgery and every six months for the next 2 years.

**Discussion:**

Among Siewert II AEG patients with resectable tumors, this is the first prospective, randomized clinical trial comparing the surgical safety of minimally invasive RTA and TH. RTA is hypothesized to provide better digestive tract reconstruction and dissection of mediastinal lymph nodes while maintaining a high quality of life and good postoperative outcome. Moreover, this trial will provide a high level of evidence for the choice of surgical procedures for Siewert II AEG.

**Clinical trial registration:**

Chinese Ethics Committee of Registering Clinical Trials, identifier (ChiECRCT20210635); Clinical Trial.gov, identifier (NCT05356520).

## Background

Adenocarcinoma of the esophagogastric junction (AEG) is defined as a tumor with an epicenter within 5 cm of the esophagogastric junction (EGJ) (1). Over the past two decades, the incidence of AEG has increased significantly, accounting for 5-8% of esophageal cancer in China and 35.7% of gastric cancer and lower esophageal cancer around the world (2–4). Siewert and Stein divided AEGs into three categories based on the distance between the tumor center and the EGJ. The epicenter of a tumor that measures between 1 and 5 cm above the EGJ is defined as type I, while that of an epicenter within 1 cm above and 2 cm below the EGJ is defined as type II, and those within 2–5 cm below the EGJ are defined as type III (5).

Currently, AEG is treated mainly by surgical resection. The National Comprehensive Cancer Network (NCCN) guidelines state that the management of Siewert type I should be similar to that of esophageal cancer, and the thoracoabdominal surgical approach (TA) is recommended because of its higher rate of thoracic lymph node involvement. Siewert type III should be managed as gastric cancer, and an abdominal-transhiatal surgical approach (TH) is recommended (6, 7). However, Siewert type II adenocarcinoma of the esophagogastric junction (Siewert II AEG) differs from the other two types in terms of its anatomical location and biological behavior, which is characterized by high differentiation, deep invasion, susceptibility to metastasis and adverse outcomes (8), making the proper operative approach for Siewert II AEG controversial.

To provide the most effective surgical treatment strategy for patients with Siewert II AEG, the ideal approach should not only consider primary tumor removal and local lymph node dissection but also ensure a safe and effective digestive tract reconstruction method (9). At present, some specialists prefer TA, while others prefer TH (10–12). Compared with TH, TA has a better effect on mediastinal lymph node dissection, with significant advantages for the dissection of subcarinal, paraesophageal, hilar and diaphragmatic lymph nodes (13). And TA provides more operating spaces for resection of the distal esophagus, which ensures a long enough upper resection margin distance from the tumor (10). However, TH can avoid invasion of the chest and minimize pleural complications, which is superior to transthoracic surgery in this respect. In addition, the surgical approach to TA varies in different countries. In Western countries, the right thoracoabdominal surgical approach (RTA) is preferred, whereas in Asian countries, the left thoracoabdominal surgical approach (LTA) is preferred. The results of a prospective study comparing the LTA and RTA showed that the overall number of lymph nodes removed during the LTA was inferior to the RTA, especially for abdominal lymph nodes (14). Further comparison of long-term survival studies showed that the 3-year DFS, OS and local recurrence rate of the RTA were better than those of the LTA (15). Therefore, the NCCN guidelines recommend the RTA rather than LTA for patients with Siewert II AEG (6). Nevertheless, studies have shown that thoracoscopic surgery has a higher incidence of respiratory and cardiovascular complications (16). A meta-analysis including 16 studies indicated that significantly higher incidence of cardiovascular and respiratory complications, and longer length of hospital stay were observed in the RTA group (17). As a result, RTA has certain limitations compared with TH. Thankfully, extensive use of thoracoscopy and laparoscopy in recent years could provide better surgical views and more space for radical surgery of esophagogastric junction Siewert-type adenocarcinoma. A minimally invasive surgical approach can significantly lower the incidence of cardiovascular and respiratory diseases, at the same time reduce intraoperative blood loss, speed up recovery of bowel function and contribute to early discharge compared to open surgery (18). Previous studies have shown that both the minimally invasive Ivor Lewis (RTA) procedure and the minimally invasive abdominal-transhiatal (TH) procedure are superior to open surgery in terms of safety and efficacy for patients with Siewert II AEG (19).

According to the study reported by Wee et al., the minimally invasive RTA approach mainly includes laparoscopic partial or total gastric resection, followed by thoracoscopic distal esophagotomy and mediastinal lymph node dissection (20). The study identified minimally invasive RTA as a viable and safe surgical approach with significantly lower morbidity and mortality compared to open surgery. And Wang et al. reported that minimally invasive TH approach would only be performed by laparoscopy for gastrectomy, distal esophagectomy and diaphragmatic hiatus mediastinal lymph node dissection (19). They believe that minimally invasive TH approach is also a safe and feasible approach with great prospects for clinical application. To date, there are no prospective randomized controlled trials comparing RTA with TH under minimally invasive conditions. Therefore, whether minimally invasive RTA is better than minimally invasive TH is of great research value for the improvement of clinical therapeutic effects for patients with Siewert II AEG.

Based on these points, it is necessary to compare surgical safety, oncology outcomes, and quality of life between RTA and TH for patients with resectable Siewert II AEG in a multicenter randomized controlled trial.

## Methods

### Objective

The purpose of this trial is to compare RTA with TH for resectable Siewert II AEGs based on surgical safety, clinical efficacy and prognosis. The primary outcome of the study will be the 3-year disease-free survival (DFS) to assess the oncological safety of the procedure. The secondary outcomes will be 5-year overall survival (OS), incidence of postoperative complications, postoperative mortality, local recurrence rate, number and location of removed lymph nodes, surgical Apgar score, duration of the operation and the quality of life (QOL) score.

### Study design

This is the first prospective multicenter randomized clinical trial comparing the efficacy of RTA and TH, which will be carried out in China. Centers participating in the trial will include Xi-jing Hospital, Tang-du Hospital, Henan Province People’s Hospital, General Hospital of Ningxia Medical University, First Affiliated Hospital of Xi ‘an Jiaotong University and the First Affiliated Hospital of Shanxi Medical University. The Declaration of Helsinki statement, as well as the international ethical guide to human biomedical research, form the guiding principles of this research. This study has been registered at clinical-trial.gov (NCT05356520) and approved by the Chinese Ethics Committee of Registering Clinical Trials (ChiECRCT20210635). Upon modification of the protocol, the participating institutes will be notified, and the ethics committee will need to approve it again if the change substantially affects the trial. Surgeons who are competent in both approaches will conduct this study. Throughout the study, surgeons, patients, and coordinating researchers will not be blinded to the group allocation.

### Study population

This trial will evaluate patients with Siewert II AEG whose tumors can be safely resected by both minimally invasive RTA approach and minimally invasive TH approach.

### The inclusion criteria for this study are as follows

·Siewert II AEG confirmed histologically·Both RTA and TH can safely resect the tumor·Pretreatment stage cT_1-4a_, N_0-3_, M_0_ (referring to the 8th AJCC TNM staging system)·Aged 18-75·The Eastern Cooperative Oncology Group (ECOG) performance status ranges from 0 to 2·American Society of Anesthesiologists (ASA) <4·Laboratory tests: hemoglobin > 90 g/L, white blood cells > 3×10^9^/L, platelet > 100×10^9^/L, glomerular filtration rate > 60 ml/min, total bilirubin < 1.5x upper level of normal (ULN), aspartate aminotransferase (AST) and alanine aminotransferase (ALT) < 2.5x ULN·Informed consent is voluntarily signed by the patients and their families

### The exclusion criteria are as follows

·Siewert type I and III adenocarcinoma of the esophagogastric junction confirmed histologically·A tumor that extends more than five centimeters from the EGJ or has developed distant metastases (M1) or peritoneal invasion·Significant cardiovascular disease, such as coronary atherosclerosis or myocardial infarction, with symptoms in the past 6 months·Significant respiratory disease, defined by whether the forced expiratory volume in 1 second (FEV1) is less than 1.5 L/s·History of right thoracotomy, adhesions to the right pleura or prior epigastric surgery·Indocyanine green test is not less than 15% for significant cirrhosis or chronic liver disease·Overt central nervous system disorders, mental disorders, and psychological disorders·Significant coagulopathy that has not been modified by current technology·Significant endocrine disorders, such as uncontrolled diabetes·A disease that is seriously out of control, such as a recurrent infection·Tumor-related diseases that require emergency surgery due to special conditions such as bleeding, perforation and obstruction

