### The termination test standards are as follows

Patients will be terminated if any of the following conditions occur, and the study analysis will not include data from these individuals:

·Patients who are found to be inoperable for a variety of reasons after trial registration (the reasons should be documented in detail)·The investigator considers the patient unfit for further participation in the study (reasons for withdrawal should be recorded in detail)·The patient requests termination of the trial·The patient violates the treatment principles (violating the admission criteria, disobeying the study arrangements, etc.)

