### Patient screening

**Figure 1** displays the trial flow. Before enrolling a patient, a comprehensive assessment will be performed to determine whether the patient meets the enrollment criteria. The results of the endoscopy and pathological analysis will be used to determine whether the classification criteria of Siewert II AEG are met. CT, enhanced CT, MRI, PET-CT and endoscopy will be used to identify and judge the tumor infiltration depth and the possibility of distant metastasis. A physical examination and laboratory tests for the patients are also essential screening methods. In addition, the medical history and basic demographics should be included in the complete preoperative work-up.

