### Patient inclusion and randomization

After all of the patients have completed the baseline assessment, they will be reviewed on a case-by-case basis according to the trial’s inclusion and exclusion criteria. Subsequently, an opaque envelope will be unsealed by a research assistant who is not involved in the recruitment and review of patients. This envelope contains a random number table for randomly assigning people who meet the trial requirements to either the RTA or TH group. The patients and surgeons cannot be blinded to their assignment, whereas the pathologists will be blinded to the patient’s group assignment.

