### Intervention

An equal number of patients will be randomly assigned to the RTA and TH groups. Details of the surgery are determined by the surgeons at each center as long as the tumor can be resected completely. If the tumor is difficult to be resect under minimally invasive conditions, the surgical strategy will be adjusted at that time.

The TH approach will be performed by distal esophagectomy and mediastinal lymph node dissection *via* the diaphragmatic hiatus under laparoscopy, whereas the RTA approach will be performed under thoracoscopy. The resection margin is a key indicator for evaluating the curative effect of surgery. The 5-year mortality of patients with positive resection margins is significantly higher than that of patients with negative resection margins (21).

According to the NCCN guidelines (6) and the Chinese expert consensus, for Siewert type II AEG with cT1 stage, the upper esophageal resection margin is recommended to be at least 2 cm away from the tumor, while for patients with cT2 stage or above, the upper esophageal resection margin is recommended to be at least 5 cm away from the tumor if the RTA approach is performed and at least 3 cm if the TH approach is performed. For patients in the former staging category, the lower resection margin is recommended to be at least 3 cm, while for patients in the latter staging category, a minimum of 5 cm is required to meet the surgical requirements. Laparoscopic proximal gastrectomy can be performed regardless of the surgical approach if the above criteria for the lower resection margin are met and at least more than half of the residual stomach remains.

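### The right-pleural-adhesion exclusion is not limited to adhesions known before randomisation, so with the termination rule it can remove RTA patients from the analysis while comparable TH patients stay in

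*Protocol article*

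**What the plan says.** All places are in the protocol article.

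- **Exclusion criteria.** One item reads "History of right thoracotomy, adhesions to the right pleura or prior epigastric surgery". It names neither a means nor a time of establishing the adhesions.
- **Patient screening.** Before enrolment, "a comprehensive assessment will be performed to determine whether the patient meets the enrollment criteria". The imaging and endoscopy listed there "will be used to identify and judge the tumor infiltration depth and the possibility of distant metastasis"; the pleura is not mentioned. Medical history is part of the work-up, and Table 1 schedules an enhanced thoracic CT before operation.
- **Patient inclusion and randomization.** Eligibility is reviewed case by case. "Subsequently, an opaque envelope will be unsealed by a research assistant who is not involved in the recruitment and review of patients". Surgeons and patients are not blinded.
- **Intervention.** TH is done by laparoscopy through the hiatus, "whereas the RTA approach will be performed under thoracoscopy". The Background adds that TH spares the chest.
- **Termination test standards.** "Patients will be terminated if any of the following conditions occur, and the study analysis will not include data from these individuals". One trigger is "The patient violates the treatment principles (violating the admission criteria, disobeying the study arrangements, etc"; another is "Patients who are found to be inoperable for a variety of reasons after trial registration".

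**The concern.** A post-randomisation exclusion is tolerable only if the fact behind it predates randomisation and has the same chance of being discovered in both arms. Prior thoracotomy and prior epigastric surgery can be known from history in every patient. Pleural adhesions that neither history nor CT has revealed are different: the RTA surgeon will see them and the TH surgeon normally will not.

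On its own this would be untidy wording. It matters because the termination standards attach a consequence to a late-found breach of the admission criteria, namely loss of the patient's data. The analysed RTA arm could then lack patients with adhesions while the analysed TH arm still contains them. If such patients do worse, RTA would look better than it is on complications and operating time (both secondary outcomes) and possibly on 3-year DFS, in an open-label trial that aims to compare surgical safety.

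**Working it through.** **Step 1. Follow the same patient through each arm.** Take a patient with right pleural adhesions that history and baseline CT did not reveal.

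| Stage | Assigned to RTA | Assigned to TH |
|---|---|---|
| Eligibility review before the envelope | passes | passes |
| Operation | right chest viewed by thoracoscopy; adhesions seen | laparoscopy through the hiatus; right chest not routinely viewed |
| Exclusion item, read literally | breached | breached, but nobody knows |
| Termination rule | can be terminated and left out | stays in |

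The rule plainly acts on patients already enrolled: it speaks of termination, and its inoperability trigger refers to the time after registration.

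**Step 2. Inputs for the size.** The documents give no figure for this effect, so there is none to reproduce.
- From Sample size calculation: 106 per arm; 15% dropout, so 106 × 0.85 ≈ 90 evaluable per arm; DFS 47.6% and 32%, mean (47.6 + 32)/2 = 39.8%; one-sided 5% test.
- Assumed: share *f* of the RTA arm removed, 3-10% (wider range 2-15%); deficit *d* of removed against retained RTA patients, 20 points (wider range 10-30).

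**Step 3. Patients affected.** 106 × 0.03 = 3.2 and 106 × 0.10 = 10.6, so about 3 to 11 RTA patients and about none in TH.

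**Step 4. Shift.** If retained patients have success rate *r*, the whole arm has (1 − f)·r + f·(r − d) = r − f·d. Dropping the affected patients therefore raises the RTA rate by f·d:
- f = 3%, d = 20: 0.03 × 20 = 0.6 points
- f = 10%, d = 20: 0.10 × 20 = 2.0 points
- wider range: 0.02 × 10 = 0.2 to 0.15 × 30 = 4.5 points

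The formula is the same for an adverse outcome such as a complication, where the RTA rate falls by f·d.

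**Step 5. What this does to the test if the arms truly have equal DFS.** By normal approximation, the actual one-sided error is 1 − Φ(1.645 − f·d/SE), with SE = √[0.398 × 0.602 × (1/(90(1 − f)) + 1/90)]. For f = 10% and d = 20 points, SE = √[0.2396 × (1/81 + 1/90)] = 0.0750. Then 0.020/0.0750 = 0.267, and 1 − Φ(1.378) = 8.4%.

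| f | d = 10 | d = 20 | d = 30 |
|---|---|---|---|
| 2% | 5.3% | 5.6% | 5.9% |
| 5% | 5.7% | 6.6% | 7.5% |
| 10% | 6.5% | 8.4% | 10.7% |
| 15% | 7.4% | 10.6% | 14.6% |

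With every randomised patient kept in the assigned arm, f = 0 and this bias vanishes.

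**The case against.** The best defence is that the item is a preoperative one. It opens with history and sits between two history items, so it can be read as known adhesions. Eligibility is reviewed before the envelope is opened, and Table 1 ticks inclusion and exclusion once, at preoperation. Nothing tells sites to recheck eligibility in theatre. The Intervention section deals with difficult operations by adjusting the strategy or converting, and does not call that ineligibility. How each exclusion is ascertained is also something an article may leave to the full protocol.

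Much of this stands. Silence on the method of ascertainment is not the point here. The point is that two stated rules, taken at their words, combine badly. The termination rule is not confined to breaches that could have been known beforehand, and six centres could read the item differently.

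A reader might go further in four ways that the documents do not support:
- **That adhesions can be found only by entering the chest.** Medical history and the baseline thoracic CT will show some. How many they miss is surgical judgement, not in the text.
- **That the fault would survive an intention-to-treat analysis.** That needs an allowance for dropping patients found ineligible later, beyond the termination rule, and the article contains none. The harm runs through the termination rule; without it, a late-found adhesion is a deviation in a retained patient.
- **That the bias must favour RTA.** That holds only if the removed patients do worse, which is plausible for complications and operating time and less certain for DFS.
- **That RTA would be flattered on conversion.** Conversion is not a listed outcome.

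**Conclusion.** The point holds in a limited form. As worded, the exclusion item and the termination rule together permit an exclusion after randomisation that can in practice fall on one arm only, triggered by a finding of an unblinded surgeon. The documents do not show that sites will apply them this way.

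On the central assumptions the shift is 0.6-2.0 points toward RTA, against a planned DFS contrast of 47.6 − 32 = 15.6 points; the extreme of the wider range is 4.5 points. Frequency, deficit and direction are all assumed, and the error rates further assume that these removals come on top of the 15% dropout. The effect is probably small, but it is systematic, a larger sample would not remove it, and it is cheap to prevent. It should be corrected.

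**What to change.** 1. Word the exclusion item as right pleural adhesions known or documented before randomisation, from history or from the baseline thoracic CT already in Table 1.
2. State that eligibility is fixed at randomisation.
3. Amend the termination standards so that adhesions first seen at operation are recorded as an operative finding, not as a breach of the admission criteria, and the patient is followed and analysed in the assigned arm.

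The cost is a few lines of text and no new tests. Some RTA patients with unsuspected adhesions will remain in the analysis, which may make the RTA results slightly less favourable. These wording changes leave the conduct of the operation untouched.

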### The termination test standards are as follows

Patients will be terminated if any of the following conditions occur, and the study analysis will not include data from these individuals:

·Patients who are found to be inoperable for a variety of reasons after trial registration (the reasons should be documented in detail)·The investigator considers the patient unfit for further participation in the study (reasons for withdrawal should be recorded in detail)·The patient requests termination of the trial·The patient violates the treatment principles (violating the admission criteria, disobeying the study arrangements, etc.)

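### The plan deletes the data of patients terminated after an open-label, preoperative randomisation, so the primary DFS comparison is no longer a comparison of the randomised groups

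*Protocol article*

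**What the plan says.** The protocol article, under *The termination test standards are as follows*, states an analysis rule: "Patients will be terminated if any of the following conditions occur, and the study analysis will not include data from these individuals". Four grounds follow:

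- "Patients who are found to be inoperable for a variety of reasons after trial registration"
- "The investigator considers the patient unfit for further participation in the study"
- "The patient requests termination of the trial"
- "The patient violates the treatment principles (violating the admission criteria, disobeying the study arrangements, etc", an open-ended list.

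*Patient inclusion and randomization* places allocation after the baseline and eligibility review: "After all of the patients have completed the baseline assessment, they will be reviewed on a case-by-case basis". Table 1 ticks randomisation in the preoperation column. *Study design* says that surgeons, patients and coordinating researchers are not blinded. *Intervention* lets participants stop at any time during the study.

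*Statistical analysis* names no analysis population, and intention-to-treat is not mentioned anywhere in the article.

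**The concern.** Randomisation protects the comparison only if the groups analysed are the groups randomised. Here patients can leave the analysis because of events that follow allocation: a finding at operation, a later judgement of unfitness, non-adherence or withdrawal. Everyone who can trigger such a removal knows the arm, and the unfitness ground has no objective criterion.

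The two operations differ, so removals may differ between arms in number or in prognosis. Patients found inoperable would be expected to do badly on DFS, the primary outcome, so an arm that loses more of them would look better than it is.

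The rule also discards information. A patient who asks to stop in the second year has contributed event-free follow-up, or perhaps an event. Read as written, the rule deletes that record, where censoring would keep it.

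**Working it through.** **Order of events.** Baseline work-up, eligibility review, randomisation (preoperation column of Table 1), surgery, follow-up to 60 months. Inoperability seen at surgery, later unfitness, withdrawal during follow-up and disobeying study arrangements all come after randomisation. Two cases are less clear. The inoperability ground runs from registration, which the article does not place relative to randomisation. A breach of the admission criteria concerns baseline status, even if it is discovered later. So most of the removals, not necessarily all, can follow allocation.

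**Inputs from *Sample size calculation*.** 106 patients per arm, one-sided 5% error, 3-year DFS of 47.6% for the right thoracoabdominal approach (RTA) and 32% for the transhiatal approach (TH). The mean is (47.6 + 32)/2 = 39.8% and the planned difference is 47.6 - 32 = 15.6 points.

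**Assumptions, not in the documents.** True 3-year DFS is p = 39.8% in both arms. A share x of an arm is removed, and those removed have DFS q. The test is approximated by a normal comparison of two proportions.

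**Formulas.**

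- DFS among those analysed = (p - xq)/(1 - x)
- Analysed n = 106(1 - x)
- SE = sqrt[a(1 - a)/n_a + b(1 - b)/n_b], where a and b are the analysed DFS in the two arms
- One-sided error = P(Z > 1.645 - (a - b)/SE)

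**Worked case.** 10% removed from RTA, 5% from TH, q = 0:

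- a = 0.398/0.90 = 0.442 and b = 0.398/0.95 = 0.419, so the difference is 2.3 points
- n = 95.4 and 100.7, SE = 0.0707, shift = 0.0233/0.0707 = 0.33
- error = P(Z > 1.645 - 0.33) = 9.4%

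**Range.**

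| Removed, RTA vs TH | DFS in those removed | False difference (points) | One-sided error |
|---|---|---|---|
| 15% vs 15% | 0-20% | 0 | 5.0% |
| 10% vs 5% | 0-20% | 1.2-2.3 | 6.9-9.4% |
| 15% vs 5% | 0-20% | 2.5-4.9 | 9.6-16.9% |
| 10% vs 0% | 0-10% | 3.3-4.4 | 12.1-15.6% |
| 15% vs 0% | 0-10% | 5.3-7.0 | 18.4-25.7% |
| any | 39.8% (same as the rest) | 0 | 5.0% |

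In the first row the contrast is unbiased, but both DFS estimates rise from 39.8% to 43.3-46.8%. If TH loses more patients, the same differences favour TH. The one-sided error then falls below 5%, and the trial loses power to show a benefit of RTA.

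**The case against.** The strongest reply is that the documents do not show unequal removal. They give no rates by arm, and with equal rates and equal prognosis the comparison under the null is unbiased. This stands. It limits the point to a loss of protection, with a bias of unknown size and sign.

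A reader might infer more, and the text does not support it:

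- **That the removal is differential by design.** The exclusion criteria list "History of right thoracotomy, adhesions to the right pleura or prior epigastric surgery". One could argue that pleural adhesions come to light only when the right chest is entered, and so remove RTA patients alone. No section says when adhesions are detected, so this rests on surgical knowledge from outside the article. Nor does anything say that such patients have worse DFS, and if theirs were average the bias would be zero. The same criterion includes prior epigastric surgery, and the RTA operation also has a laparoscopic phase (*Background*), so abdominal findings can arise in both arms.
- **That converted patients are deleted.** *Intervention* says "If the tumor is difficult to be resect under minimally invasive conditions, the surgical strategy will be adjusted at that time" and allows conversion to open surgery. The termination list names neither conversion nor crossover. Whether they count as violations is undefined.
- **That the analysis becomes as-treated.** Nobody is reassigned by the operation received. The resulting set is closer to a per-protocol set.
- **That the 15% dropout rate supports the one-arm scenarios.** That rate is not specific to an arm. Loading it all onto one arm is the upper end of the illustration.

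It could also be said that analysis populations belong in an analysis plan that is not shown. That would answer a silence. Here the article states the exclusion itself.

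**Conclusion.** The rule is wrong as written. It removes randomised patients on partly discretionary, unblinded grounds, mostly after allocation, and discards follow-up already collected. The DFS comparison then loses the protection of randomisation.

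That conclusion rests on the text alone. The size does not: it depends on the assumed removal rates and on the DFS of those removed. Moderate imbalance (10% vs 5%) costs 1.2-2.3 points, and 15% vs 5% costs 2.5-4.9 points, against a planned effect of 15.6 points. If RTA is the arm losing more, the one-sided error is 6.9-9.4% and about 9.6-17% respectively. Removal of 10-15% from RTA alone, with DFS of 0-10% in those removed, is the extreme at 12-26%. With balanced removal the error stays at 5%, but both DFS estimates are too high.

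**What to change.** Change the analysis rule only. The clinical reasons for stopping study treatment need not change.

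1. Replace the exclusion sentence with: all randomised patients are analysed in the arm assigned.
2. Separate stopping study treatment from stopping follow-up. Keep following terminated patients, and censor only at withdrawal of consent to follow-up or at loss to follow-up, keeping everything collected before that date.
3. State in advance, identically for both arms, how patients found unresectable count for DFS. One option is an event on the day of the finding, with time counted from randomisation. Other conventions are possible.
4. Keep the present exclusions as a per-protocol sensitivity analysis.

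The cost is wording, continued follow-up of a few enrolled patients, and some power. The stated 90% is not a usable baseline. With the article's own rates, 106 per arm gives 75.3% one-sided, or 69.1% with 90 per arm left after 15% loss (the sample size is a separate point). Suppose that 5-15% of each arm have a DFS of 10-20% whatever the approach, and are kept. The diluted rates are (1 - x) × 47.6% + xq and (1 - x) × 32% + xq. Power with 212 patients is then about 64-72%, and 90% one-sided power needs 366-450 analysed patients, against 334 (2 × 167) without dilution. This should enter the calculation when the power is restated. The change is best made soon, since follow-up not collected on terminated patients may not be recoverable.
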